# The Philani MOVIE study: a cluster-randomized controlled trial of a mobile video entertainment-education intervention to promote exclusive breastfeeding in South Africa

**DOI:** 10.1186/s12913-019-4000-x

**Published:** 2019-04-02

**Keywords:** Mobile health, Video, Narrative, Entertainment-education, Community-based, Community health worker, Human-centered design, Maternal child health behavior, Breastfeeding, South Africa

## Abstract

**Background:**

In South Africa, rates of exclusive breastfeeding remain low and breastfeeding promotion is a national health priority. Mobile health and narrative entertainment-education are recognized strategies for health promotion. In-home counseling by community health workers (CHWs) is a proven breastfeeding promotion strategy. This protocol outlines a cluster-randomized controlled trial with a nested mixed-methods evaluation of the MObile Video Intervention for Exclusive breastfeeding (MOVIE) program. The evaluation will quantify the causal effect of the MOVIE program and generate a detailed understanding of the context in which the intervention took place and the mechanisms through which it enacted change. Findings from the study will inform the anticipated scale-up of mobile video health interventions in South Africa and the wider sub-Saharan region.

**Methods:**

We will conduct a stratified cluster-randomized controlled trial in urban communities of the Western Cape, to measure the effect of the MOVIE intervention on exclusive breastfeeding and other infant feeding practices. Eighty-four mentor-mothers (CHWs employed by the Philani Maternal Child Health and Nutrition Trust) will be randomized 1:1 into intervention and control arms, stratified by neighborhood type. Mentor-mothers in the control arm will provide standard of care (SoC) perinatal in-home counseling. Mentor-mothers in the intervention arm will provide SoC plus the MOVIE intervention. At least 1008 pregnant participants will be enrolled in the study and mother-child pairs will be followed until 5 months post-delivery. The primary outcomes of the study are exclusive breastfeeding at 1 and 5 months of age. Secondary outcomes are other infant feeding practices and maternal knowledge. In order to capture human-centered underpinnings of the intervention, we will conduct interviews with stakeholders engaged in the intervention design. To contextualize quantitative findings and understand the mechanisms through which the intervention enacted change, end-line focus groups with mentor-mothers will be conducted.

**Discussion:**

This trial will be among the first to explore a video-based, entertainment-education intervention delivered by CHWs and created using a community-based, human-centered design approach. As such, it could inform health policy, with regards to both the routine adoption of this intervention and, more broadly, the development of other entertainment-education interventions for health promotion in under-resourced settings.

**Trial Registration:**

The study and its outcomes were registered at clinicaltrials.gov (#NCT03688217) on September 27th, 2018.

## Background

Despite global progress in reducing maternal, newborn and child mortality, more than 5 million children, around the world, die before reaching their fifth birthday [1]. Rates of under-5 mortality are highest in sub-Saharan Africa and, in 2015, 45% of these deaths occurred in newborns. A majority of under-5 deaths are the result of preventable diseases, the incidence of which could be reduced by implementing health-promoting maternal-child behaviors, such as exclusive breastfeeding (EBF) [1–4].

The health benefits of EBF, especially in low- and middle-income countries (LMIC), have been well documented [5]. For the child, these include protection against infectious diseases, improved measures of intelligence and decreased risk of becoming overweight and developing diabetes. EBF also confers health benefits for the mother, including a reduced risk of breast and ovarian cancer [5]. Globally, EBF could save an estimated 823,000 under-5 lives each year, as well as preventing 20,000 maternal deaths from breast cancer. Yet, despite World Health Organization recommendations that children should be exclusively breastfed for the first 6 months of life, EBF rates hover at only 37% in LMIC [5].

South Africa has one of the lowest rates of EBF in the world [5]. Estimates of EBF rates under-6 months in South Africa range from 8% [5, 6] to the most generous estimate, 32% [7]. Furthermore, the percentage of children exclusively breastfed appears to decrease sharply over the first 6 months, from 44% of infants aged 0–1 month to 24% of infants aged 4–5 months [7]. The health problems that result are largely due to unsafe formula feeding and the widespread practice of introducing solid foods early (often before 3 months) into the infant’s diet [8]. In South Africa, some reports suggest that more than 70% of infants are given solid foods before reaching 6 months, the recommended age for initiating complementary feeding [8]. Unsafe formula feeding, including the use of bottles with poorly cleaned nipples, can lead to diarrheal disease [9] from pathogens entering the gut. Solid foods, introduced too early into a child’s diet, can also cause gastro-intestinal infections as well as nutrient deficiencies when these foods displace breastmilk without providing adequate nutrient density [10]. The limited availability of reliable national data on infant feeding in South Africa complicates the design and evaluation of infant feeding interventions [8]. However, systematic reviews of the literature suggest that large-scale interventions focused on educating mothers can increase the prevalence of EBF and decrease infant mortality [11–14].

The narrative entertainment-education (E-E) approach to health education appears to be a promising strategy for promoting health behavior change [15, 16]. E-E content endeavors to deliver health messaging through an entertainment media framework. A growing body of scientific evidence suggests that E-E is an effective approach towards positively influencing beliefs, attitudes and behaviors [15, 17–20]. Especially in populations with low motivation and/or a reduced ability for cognitively evaluating the intended health messaging, E-E may be a powerful health education strategy [15]. The characteristics of effective E-E include: a) appealing narratives, b) high production quality, c) persuasive messages that are unobtrusive and d) high potential for involvement or identification with the presenters or characters portrayed [15]. While E-E can take many forms, a video-based approach readily supports the harmonious integration of these characteristics.

Video-based content, optimized for mobile devices, may also facilitate broad dissemination of health education, especially as the global penetration of mobile technology increases. Recent advances in mobile messaging have already begun to facilitate the delivery of health messages at scale [21–23] and researchers are increasingly recognizing the potential for mobile phones and tablets to play an important role in health education interventions in LMIC [23–26]. South Africa is an example of a LMIC at the forefront of mobile health (mHealth) initiatives, due to its rapidly expanding penetration of mobile phones and national internet infrastructure [27–29]. National, maternal-child mHealth initiatives built around free, text-based SMS messaging have attracted global attention and been well received [30, 31]. General “tech-savviness” in South Africa continues to grow, with 37% of adults reporting smartphone ownership and 42% reporting daily internet usage in 2016 [32]. Active experimentation with WhatsApp, a widely used mobile communication tool that supports the transfer of videos, is also underway in many sectors, including health [33, 34].

Even for South Africans who do not yet have access to mobile phones, a feasible dissemination pathway lies in the delivery of educational videos by community health workers (CHWs) who bring teaching tablets to their in-home counseling sessions [35]. Interventions that support women in their homes have demonstrated efficacy in improving breastfeeding rates [36]. The Philani Maternal Child Health and Nutrition Trust [37] is an example of a successful community based organization, employing “mentor-mothers”, CHWs who offer in-home health promotion counseling to pregnant women and mothers within their neighborhoods. Data from both case studies and quantitative research suggest additional improvements in breastfeeding rates when synergistic interventions – for example, mass media interventions – are used to supplement successful community-based programs [36]. Developing interventions that boost the efficacy of community-based programs may be a critical step towards ending preventable child and maternal deaths by 2030 (as called for by the World Health Organization and UNICEF) [38]. Prior research in South Africa suggests that such synergistic interventions are even more effective when they are created in close collaboration with community-based programs, actively involving local stakeholders in the content creation process [39].

Applying a human-centered design (HCD) approach to the development of health education interventions may be a powerful way of tailoring these interventions to the specific settings and needs of their target communities, a priority identified in the 2016 *Lancet* Series on Breastfeeding [36]. The HCD approach has been described as “constructive, experiential and rooted in the needs and context of end-users of a product or service” [40], with the end goal of developing novel solutions to pressing problems. The creation of health education using an HCD approach involves several principles and practices that have been well characterized in the literature [41]. These include focusing on an empathic understanding of the target audience, creating content through a process of rapid prototyping, gathering of feedback and responsive iteration. Finally, the HDC approach is characterized by a relatively high tolerance for ambiguity and failure during the design process [40, 42].

Recent systematic reviews of mHealth interventions for improving maternal and neonatal health outcomes have called for: 1) strong experimental research designs including randomized controlled trials, 2) feasibility research, 3) government involvement and 4) integration of mHealth interventions into the healthcare system [23]. The Philani MOVIE intervention will be evaluated using a randomized-controlled trial, which follows a successful, qualitative feasibility study [35] involving the same population of CHWs who will be delivering the intervention in this trial. The 13-video Philani MOVIE intervention was created in collaboration with the Western Cape Department of Health, the South African National Department of Health, the Philani Maternal Child Health and Nutrition Trust and UNICEF, among other local stakeholders. By integrating the Philani MOVIE intervention into the successful, community-based Philani Mentor Mother Outreach Program [37], we aim to explore the potential for innovative, mobile video interventions to positively impact breastfeeding rates in South Africa, an important predictor of maternal and neonatal health outcomes.

### Aims

This study will achieve the following specific research aims: ToEstablish theEffectiveness of the Philani MOVIE intervention for increasing the practice of exclusive breastfeedingEffectiveness of the Philani MOVIE intervention for improving other infant feeding practices and maternal knowledge about infant feedingDetermine the usefulness of human-centered design principles when applied to the development of mobile health interventionsElucidate the mechanisms of intervention action and the acceptability of the intervention to CHWs.

## Methods

### Study setting and implementation partner

This study will be conducted within the under-resourced settlements of the Western Cape Province in South Africa. In 2010, the infant mortality rate in the Western Cape was reported to be 25 per 1000 live births [43]. A 2014 study of under-resourced communities in the Western Cape, found the EBF rate to be only 6% [44]. Operating within these communities (see Fig. 1), the Philani Maternal Child Health and Nutrition Trust [37] is a non-government organization serving approximately 100 under-resourced neighbourhoods. The Philani Mentor Mother Outreach Program is focused on improving child health outcomes through the deployment of “mentor-mother” CHWs. Mentor-mothers are identified as positive role models within their communities, after they have demonstrated success in raising healthy families despite resource shortages. Once recruited, mentor-mothers complete a standardized training program for delivering in-home health promotion counselling services within their communities. Among other health-promotion tasks, Philani mentor-mothers are trained to monitor growth, counsel parents around proper nutrition and refer sick family members to the nearest clinic when necessary. These mentor-mothers promote a variety of health behaviours, including those related to HIV-prevention, breastfeeding, child nutrition, growth and development [37, 45, 46].

**Fig. 1 Fig1:**
[figure not shown]
Regions of Operation of the Philani Maternal Child Health and Nutrition Trust, Western Cape, South Africa. (Illustrations by [name]. Map data© 2018 Google and© 2018 AfriGIS (Pty) Ltd.)

### Description of the intervention

The Philani MOVIE intervention consists of 13 short, (2-5 min.) educational videos created over the course of 10 months in collaboration with community members and local stakeholders in maternal-child health. The health messaging in each video is closely aligned with the most recent WHO recommendations for infant feeding and narrated in English and isiXhosa, the languages spoken most widely among the study participants. The videos use simple syntax, avoiding medical jargon. Table 1 summarizes the video topics included in the Philani MOVIE intervention.

**Table 1 Tab1:** Philani MOVIE video topics

1. Trailer 2. A Breastfeeding Story 3. The Benefits of Breastfeeding 4. How Breastfeeding Works 5. Breastfeeding Recommendations 6. A Kangaroo Mother Care Story 7. Common Challenges Faced by Breastfeeding Mothers 8. What Happened to the Practice of Breastfeeding? 9. Unsafe Infant Feeding Practices 10. Breastfeeding and HIV 11. Tips for Working Mothers who Breastfeed 12. When Breastfeeding Isn’t Possible 13. A Stunting Prevention Story	

### Intervention development

A human-centered design approach was applied during the development of the intervention. Formative feedback was solicited from end-users within the target audience as well as experts in multiple disciplines, including community medicine, academia, public health, media marketing and the performing arts. Scripts were collaboratively edited by content experts, who worked in parallel using Google Drive to allow for reliable version control. Early drafts of videos were then shared via WhatsApp with community members, most of whom did not use email regularly, informing a process of Rapid Iterative Testing and Evaluation [47, 48]. Feedback from community members was gathered via WhatsApp and during face-to-face “bodystorming” (physical brainstorming) sessions [47, 49] in which mentor-mothers tested the intervention through role-play activities involving mock-counseling sessions. Feedback was synthesized on a rolling basis, informing multiple iterations of the content. In this way, the health messages, language, illustrations, characters, color palate, narrative delivery style, logo and soundtrack were collaboratively and iteratively finalized over the 10-month content creation period. Key health and motivational messages were interwoven with animations created by local artists and underscored by the narratives of community mothers and South African celebrity mothers. Both community members and media marketing experts emphasized the importance of representing and celebrating South Africa’s diverse ethnic profile. This feedback shaped production decisions about both the illustrations included in the intervention and the profiles of the mothers featured in the intervention video footage. The trailer for the series can be previewed here https://youtu.be/1sss8ViPKJo [50].

### Trial design

Our study is a cluster-randomized controlled trial with baseline covariate adjustment and stratification [51] (See Fig. 1). The randomization unit is the mentor-mother. Each mentor-mother will enroll several pregnant women over the course of the trial. We conducted analyses of routine program data from these mentor-mothers and found that, among a range of available covariates, the only significant predictor of EBF was the type of neighborhood in which the mentor-mother lived and performed her health promotion duties. These neighborhood types include: informal, formal and mixed neighborhoods. We thus decided to stratify the randomization according to neighborhood type, to ensure balance of intervention versus control assignment by this covariate. Based on the existing literature [11, 52–59], we also expected that the following covariates would be associated with the primary outcome measure:participant’s number of previous childrenparticipant’s agerunning water in the homeelectricity in the homeparticipant’s employment statusparticipant’s education level

To further increase the statistical efficiency of our analysis, we thus decided to measure these covariates at baseline and adjust for them in our primary analyses, in addition to baseline neighborhood type. Randomization of the mentor-mothers was performed, using a computer-generated random allocation sequence, by faculty at Heidelberg University, Germany. The allocations were then transferred by email to Philani for implementation. Cluster randomization was preferred over individual randomization in this trial because each mentor-mother is responsible for counseling pregnant women within her neighborhood, making individual participant randomization logistically impossible without disrupting existing protocols.

**Fig. 2 Fig2:**
[figure not shown]
Trial Design for the Philani MObile Video Intervention for Exclusive breastfeeding (MOVIE) Study

#### Trial outcome measures

The outcome measures in this trial are based on the most recently published WHO indicators for the study of feeding practices in infants [64] and the most recent national infant feeding data for South Africa [7].

**The primary outcomes** will be short-term EBF (at 1 month) and long-term EBF (at 5 months). Primary outcomes will be measured using both point-in-time (24-h recall) and life-long (since birth) data, as recommended in the literature [65]. Primary outcomes data will be collected via tablet-based questionnaires and verified by follow-up telephone surveys, administered within one week of each tablet-based survey.

**Secondary outcomes** will include a) early initiation of breastfeeding (< 1 h after delivery, measured by recall on tablet-based survey at 1 month and verified by follow-up phone survey), b) *any* breastfeeding at 1 and 5 months (based on 24-h recall on tablet-based survey and verified by follow-up phone survey), c) bottle-feeding (based on 24-h recall on tablet-based survey and verified by follow-up phone survey), early introduction of complementary foods at 1 and 5 months (based on 24-h and since-birth recall, measured by phone surveys) and maternal knowledge at 1 and 5 months (measured by phone surveys).

Table 2 summarizes the quantitative outcomes that will be examined in this trial.

**Table 2 Tab2:** Outcomes for the Philani MOVIE trial

Outcome Label	Outcome Definition	Method of Measurement
A. Primary outcome		
1. Short-term exclusive breastfeeding (24-h recall)	Infant, age 1 month, was exclusively breastfed in the past 24 h	These outcomes will be measured by tablet-based surveys, adapted from the South Africa Demographic and Health Survey 2016 [7] and following the most recent WHO indicators for infant feeding practices [64]. A point-in-time or current status measurement (based on 24-h recall) is presently the most common method for measuring exclusive breastfeeding [65]. Responses to initial tablet-based surveys administered at 1 and 5 months will be verified by follow-up phone surveys, conducted by an independent, vetted phone survey research company, within one week of the initial data collection timepoint. Life-long (since birth recall) data on exclusive breastfeeding, will also be collected and verified by phone survey. Reporting indicators based on both point-in-time and life-long data has been recommended as a stronger approach than either of these in isolation [65].
2. Long-term exclusive breastfeeding (24-h recall)	Infant, age 5 months, was exclusively breastfed in the past 24 h	
B. Secondary outcomes		
1. Short-term exclusive breastfeeding (since birth recall)	Infant, age 1 month, has been exclusively breastfed since birth	
2. Long-term exclusive breastfeeding (since birth recall)	Infant, age 5 months, has been exclusively breastfed since birth	
3. Early initiation of breastfeeding	Infant was breastfed within the first hour of life (based on recall at 1 month)	This outcome will be measured in the 1 month tablet-based survey and verified by phone survey within one week of the initial data collection timepoint.
4. *Any* breastfeeding at 1 month	Infant, age 1 month, received *any* breastmilk in the past 24 h, even if not exclusively breastfed	These outcomes will be measured by tablet-based surveys at 1 month and 5 months, adapted from the South Africa Demographic and Health Survey 2016 [7] and following the most recent WHO indicators for infant feeding practices [64]. Responses to tablet-based surveys will be verified by follow-up phone surveys, conducted by an independent, vetted phone survey research company, within one week of the initial data collection timepoint.
5. *Any* breastfeeding at 5 months	Infant, age 5 months, received *any* breastmilk in the past 24 h, even if not exclusively breastfed	
6. Bottle-feeding	Infant, under 6 months of age, was fed using a bottle with a nipple in the past 24 h.	
7. Early introduction of complementary foods at 1 month (24-h recall)	Infant, age 1 month, has received complementary foods in the past 24 h.	These out comes will be measured by phone surveys at 1 and 5 months. Participants will respond to an infant feeding questionnaire, incorporating both point-in-time and life-long data, adapted from previously published infant feeding measurement tools [82–85] and informed by the WHO indicators for infant feeding practices [64].
8. Early introduction of complementary foods at 5 months (24-h recall)	Infant, age 5 months, has received complementary foods in the past 24 h.	
9. Early introduction of complementary foods at 1 month (since birth recall)	Infant, age 1 month, has received complementary foods at some point since birth.	
10. Early introduction of complementary foods at 5 months (since birth recall)	Infant, age 5 months, has received complementary foods at some point since birth.	
11. Maternal knowledge at 1 month post-delivery	Maternal knowledge of breastfeeding current recommendations and basic health principles relevant to infant feeding measured at 1 month post-delivery.	These outcomes will be measured by phone survey questionnaires on maternal knowledge about breastfeeding (developed by study team, adapted from previously published breastfeeding knowledge assessment tools [59, 86, 87]).
12. Maternal knowledge at 5 months post-delivery	Maternal knowledge of breastfeeding current recommendations and basic health principles relevant to infant feeding measured at 5 months post-delivery.	

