#### Data collection and pre-trial training

Mentor-mothers in both the intervention and control groups will undergo training on how to obtain written, informed consent, record baseline variables and collect data on infant feeding practices directly on their tablets. This data will be collected as close as possible to the 1 month and 5 months post-delivery timepoints, (+/− 2 weeks) via infant feeding questionnaires. These questionnaires have been translated into isiXhosa and audio-recorded to help overcome literacy barriers. They will be filled out directly on the tablets by the participants. To standardize the collection of data, all 84 mentor-mothers will carry tablets with the infant feeding questionnaires for the duration of the study period. Only half [42] of the tablets will be loaded with the Philani MOVIE video intervention. All mentor-mothers will be trained on how to charge, use, troubleshoot and care for their tablets. These tablets are 8″ Android devices with 16GB of storage. The videos can be played offline and questionnaires completed and stored on the tablets while a mentor-mother is conducting home-visits in areas without internet access. Once the mentor-mother re-connects to the internet, all completed questionnaires will automatically be forwarded to the local research staff, based in Cape Town, for de-identification, cleaning and analysis.

Each tablet-based survey will be followed, within one week, by a phone-based survey conducted by Social Surveys, a professional telephone research company, located in South Africa. The use of telephone surveys for verification and follow-up after initial face-to-face interviews has demonstrated significant benefits. A dual sampling frame approach (using a combination of face-to-face and telephone interviews) has been recommended for such surveys, particularly for low-income and educationally under-resourced respondents [71–73]. Computer-assisted telephone interviewing (CATI) will also be employed to enhance accuracy of data collection and reporting. All data will be de-identified by local research staff in South Africa and carefully stored in the locked, secure offices of the local research team. Only de-identified data will be shared with collaborating research partner institutions for data analysis purposes.

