Mentor-mothers in the intervention group will receive additional training on how to deliver the Philani MOVIE videos, which are designed in a modular fashion such that they can be viewed in any order, and thus tailored to the needs of the participant. Video sequencing decisions will be made by the mentor-mothers, who are trained by Philani to facilitate close alignment between health messages delivered during home-visits and the individual needs of each participant at each home visit and perinatal stage. Mentor-mothers in the intervention group will be instructed to administer each of the 13 intervention videos at least once to each participant during the study period. Video views will be tracked directly on the tablets and recorded on a paper-based tracking form by the mentor-mothers. The Philani MOVIE intervention will be delivered in parallel to the Standard Philani Perinatal Counseling Program (SoC), which includes counseling on infant feeding (see Table 3).

**Table 3 Tab3:** Topics Addressed in Standard Philani Infant Feeding Counseling Sessions

1. Maternal beliefs about feeding 2. The practice of exclusive breastfeeding 3. The benefits of breastfeeding and the composition of breast milk 4. How milk is produced and released from the breast 5. How to position and attach a baby for breastfeeding 6. How to express breast milk 7. Common feeding difficulties and breast conditions relating to breastfeeding 8. Infant feeding for HIV positive mothers 9. Safe infant feeding for women who meet have chosen not to breastfeed and meet the AFASS criteria for formula feeding (Acceptable, Feasible, Affordable, Sustainable and Safe)	

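### Both primary outcomes are self-reports on the tablet of the mentor-mother who delivered the videos, and the planned independent phone survey only verifies them

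*Protocol article*

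**What the plan says.** All references are to the protocol article.

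- **Outcome.** Table 2 (Trial outcome measures) defines the two primary outcomes as "Infant, age 1 month, was exclusively breastfed in the past 24 h" and "Infant, age 5 months, was exclusively breastfed in the past 24 h", both measured by the tablet survey.
- **Source and check.** The text of the same section says "Primary outcomes data will be collected via tablet-based questionnaires and verified by follow-up telephone surveys, administered within one week of each tablet-based survey". Table 2 adds that the tablet responses "will be verified by follow-up phone surveys, conducted by an independent, vetted phone survey research company, within one week of the initial data collection timepoint".
- **Setting.** Under Data collection and pre-trial training, mentor-mothers of both arms are trained to "record baseline variables and collect data on infant feeding practices directly on their tablets". The mothers enter the answers: "They will be filled out directly on the tablets by the participants". Audio recordings in isiXhosa help those who read with difficulty.
- **Intervention.** All 84 mentor-mothers carry a tablet with the questionnaires, and only half of the tablets hold the videos. The same section states: "Mentor-mothers in the intervention group will be instructed to administer each of the 13 intervention videos at least once to each participant".
- **Other phone data.** EBF since birth, a secondary outcome in Table 2, is also checked by phone. Complementary feeding (outcomes 7 to 10, for example "Infant, age 1 month, has received complementary foods in the past 24 h") and maternal knowledge (outcomes 11 and 12) are measured by phone alone.

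The article does not say which 24 hours the phone question covers, what counts as verified, or which answer is analysed when the two differ.

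**The concern.** EBF by recall has no objective component. The mother reports on the behaviour her mentor-mother has been promoting, on that mentor-mother's device, in the setting of the home visit. A mentor-mother who shows the videos cannot be unaware of her arm, and neither can the mother.

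Standard counselling promotes EBF in both arms, so over-reporting common to both largely cancels. The videos add promotion in one arm only. If they also strengthen the wish to give the approved answer, the increment appears as a treatment effect. A larger sample, covariate adjustment or cluster-adjusted standard errors would not reduce it. The result would be a benefit claimed on reporting rather than feeding, in a trial meant to inform scale-up. A measurement at arm's length from the mentor-mother is already planned, but for EBF its stated role is only to verify the tablet answer.

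**Working it through.** **Inputs from the article (Sample size calculation).** Control EBF is 40% at 1 month and 10% at 5 months, the intra-cluster correlation is 0.1, the baseline correlation is r = 0.30, and the significance level is 5% (taken as two-sided, since the article does not say). There are 84 clusters, so 42 per arm. The 840 women assessed make m = 10 per cluster. The stated detectable increases at 80% power are 13 and 9 points.

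**1. The plan's own figures.** Effective n per arm = 42m / {[1 + (m − 1) × 0.1] × (1 − r²)} = 420 / (1.9 × 0.91) = 242.9. The detectable differences are 12.65 points from 40% and 8.92 points from 10%, which round to the stated 13 and 9. Power is 0.821 at 13 points and 0.806 at 9 points.

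**2. False difference when the videos have no effect.** Let p be the true EBF rate in both arms. Let q be the excess, video arm over control arm, in the share of mothers not practising EBF who report that they do. The false difference is q × (1 − p). The article gives no value for q, so a range is assumed. The rejection probability uses the effective n from step 1 and assumes no over-reporting among controls.

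| q | 1 month: q × 0.60 | P(reject) | 5 months: q × 0.90 | P(reject) |
|---|---|---|---|---|
| 2% | 1.2 points | 0.06 | 1.8 points | 0.10 |
| 5% | 3.0 points | 0.10 | 4.5 points | 0.33 |
| 10% | 6.0 points | 0.27 | 9.0 points | 0.81 |
| 20% | 12.0 points | 0.76 | 18.0 points | >0.99 |

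**3. Excess that produces the whole stated difference.** At 1 month 0.13 / 0.60 = 21.7%. At 5 months 0.09 / 0.90 = 10%. The 5-month outcome is the more exposed, because nine in ten mothers could over-report.

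**4. Expected true change between tablet and call.** Four months is 4 × 30.4375 / 7 = 17.4 weeks. A steady fall from 40% to 10% implies a weekly loss of 1 − (10/40)^(1/17.4) = 7.7% of those still exclusively breastfeeding. That is 3.1 points at 1 month (0.077 × 40) and 0.8 points at 5 months (0.077 × 10). With the national figures in the Background, 44% to 24%, the weekly loss is 3.4%, or 1.5 and 0.8 points. This assumes steady loss and no return to EBF. Individual mothers may vary more from day to day, but the group rate should move by only about 1 to 3 points over a week.

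**The case against.** **The bias is assumed, not shown.** Both arms have a mentor-mother, the same questionnaire and counselling in favour of EBF, and the mother enters her own answers with audio support. This stands in part. Self-entry removes scoring by the mentor-mother, and only the increment due to the videos matters. At 1 month it would take an implausible-looking 21.7% to produce the full 13 points. But self-entry on the mentor-mother's tablet does not remove the wish to please her.

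**The phone survey already guards against this.** A reader might infer the opposite, that the call cannot verify the tablet answer because it covers a different 24 hours. The article does not support that. It does not state the phone reference period, a call within one week may come the same day, the group rate should change little over a week, and EBF since birth, with an almost fully shared recall period, is also checked by phone. The check has value. What the article does not do is use the phone answer to estimate the effect.

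**The missing discordance rule is a defect.** A reader might infer this too. Such a rule commonly sits in the full protocol or analysis plan, which are not shown, so the point does not rest on it.

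**EBF by tablet and complementary feeding by phone contradict each other.** They need not. An infant exclusively breastfed on one day can receive food some days later. The split shows only that the phone survey is trusted as sole source for closely related outcomes.

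**The phone is not clearly the better primary source.** This stands. The mother still knows what she was shown, some women will not be reached, and filling gaps with tablet answers mixes modes. The outcomes are registered, and randomization is described as done. Replacing the primary source is therefore a debatable trade-off. Analysing the phone answer alongside it is not.

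**Conclusion.** The point holds as an exposure to arm-dependent reporting bias, not as proof of bias or of a worthless check. The plan places both primary outcomes where social desirability may act more strongly in one arm, and gives the independent interview no stated role in the EBF effect estimate.

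The size depends wholly on q, which the documents do not give. At 2% the bias is under 2 points at either time and matters little. At 5% the 5-month outcome has about a one-in-three chance of a false positive. At 10% the false difference equals the 9-point target at 5 months, but is 6 of 13 points at 1 month. These figures assume no true effect, the article's control rates and intra-cluster correlation, and a two-sided 5% test.

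**What to change.** 1. Include the 24-hour EBF question in each phone survey, state the 24 hours it refers to, and do not tell interviewers the arm.
2. Pre-specify an analysis of EBF by the phone answer with the same model and covariates as the primary analysis. It may become the primary source. At minimum it should be a key sensitivity analysis that must agree with the tablet result in direction and size before a benefit is claimed. State beforehand what agreement in size means.
3. Run the tablet analysis again in the women who also have a phone answer, so that a gap between sources is not confused with phone non-response.
4. Report by arm the phone completion rate and tablet-phone agreement. Among mothers whose phone answer is not EBF, show the share whose tablet answer was EBF. The arm difference in that share is the nearest observable counterpart of q, though it also contains true change and error in the phone answer.

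**Cost.** The phone survey is already planned, so the change is mainly wording, with at most an added question. Women not reached are missing from the phone analysis or rely on their tablet answer, and any such fallback should be counted by arm. If the question covers the 24 hours before the call, the recall day shifts by up to a week. Making the phone answer primary would also mean updating a registered outcome definition. The sensitivity-analysis version avoids that. Either version reduces the reporting bias without removing it.
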